## 9. Potential Risks:

Lumbar puncture: There is some discomfort during the lumbar puncture procedure. After a brief sting from the numbing medication, the subject will feel mostly pressure or occasionally tingling sensations. The most common side effects of a lumbar puncture are headache, nausea, vomiting, or fever. In our experience, approximately 1 % of patients undergoing a lumbar puncture can develop a refractory headache (positional). Most post LP headaches respond to lying flat and resting for 48 hours and drinking plenty of fluids and caffeinated beverages as tolerated. By definition, they are refractory if they fail to resolve after these measures are taken and an autologous blood patch performed by anesthesia or neuroradiology is the treatment of choice for immediate resolution.

Blood draw: Blood draws, and infusions may cause discomfort, pain, and bruises at the site where blood is taken and sometimes causes people to feel lightheaded or to faint.

MRI scanning: All participants will be screened for metallic implants incompatible with the MRI environment. If a patient experiences unbearable claustrophobia inside MRI scanners, he/she will be removed from the scanner.

Cognitive, neurologic, and physical exams and history: These are administered by medical professionals. However, there may be some subjects embarrassed or anxious due to the questions that must be answered.

Acute immune reactions: The PI will ensure that appropriate best clinical practices and treatment are initiated should an event indicating an allergic or hypersensitive reaction occur. If this occurs, the infusion will be stopped immediately, and the subject closely monitored until stable. The suggested treatment will depend upon the grading of the reaction (NCI-CTCAE criteria). The PI will have the support of the emergency response teams from the hospital as needed. After the infusion, patients will be continuously monitored for 4 more hours, and a full neurological physical examination will be performed before discharging the patients. In case of a severe adverse event,

we can get an assessment in regards to the continuation of the study from our DSMB within 24-48 hours.

Confidentiality: There is a possible risk of breach of confidentiality. Records with the subject's name will be maintained in the CRU charts. A database with identifiers will be maintained by the coordinator for scheduling purposes only, and will not contain any study results. All data will be kept in a password protected Redcap database. The tapes with the MDS-UPDRS section III will be kept in a locked office and the patients/subjects are not identified by name or any other identifying features.

## 10. Study schedule

The study will last a total of one year and 8 months (88 weeks) per patient (3 groups) and will include 11 clinical visits and 10 telephone evaluations (*Please see section 10.3 for the study timeline and 10.4 for study schedule*).

There are 6 types of clinical visits: Screening, Baseline, Infusion, Safety and Clinical assessment, unscheduled visit, and final visit plus phone call evaluations starting after the first infusion.

- Visit #1 Screening Visit (between week -12 to week -3): after signing the consent and discussing the purpose and timeline of the study, the PI will confirm the PD diagnosis and establish the current disease stage. At this visit, the CRU staff will collect blood for laboratory assessment. The purpose of this visit is to ensure that the patient meets the inclusion and exclusion criteria.
- Visit #2 Baseline visit (between week -11 to week-1): the purpose of this visit to obtain baseline measurements on serum, plasma, CSF, and neuroimaging.
- Visit #3 Infusion Day (week 0): First IV MSCs infusion.
- Visit #4 Clinical and Safety assessment (week 9+/-1.5 week): the purpose of this visit is to determine the safety and the immediate immunological, physical and neurological response to the first infusion.
- Visit #5 Infusion Day (week 18+/-1 week): Second IV MSCs infusion.
- Visit #6 Clinical and Safety assessment (week 27+/-1.5 week): the purpose of this visit is to monitor safety and the immunological, physical and neurological response to the second infusion.
- Visit #7 Infusion Day (week 36+/-1 week): Third IV MSC infusion
- Visit #8 Clinical and Safety assessment (week 40+/-1.5 week): the purpose of this visit is to monitor the safety and the immunological, physical and neurological response to the third infusion. Additionally, to collect enough data for our first interim analysis.

- Visit #9 Clinical and Safety assessment (week 49+/-1.5 week): the purpose of this visit is to monitor the safety and the immunological, physical, and neurological response to the infusions.
- Visit #10: Clinical and Safety assessment (week 62+/-1.5 week): the purpose of this visit is to monitor the safety and the immunological, physical, and neurological response to the infusions.
- Visit # 11: Final visit (week 88+/-1.5 week): the purpose of this visit is to determine the physical and neurological response to the complete MSC treatment.
- Unscheduled visit (between 2 to 15 days after reporting a non-live treating AE related to the MSC infusion): the purpose of this visit is to fully assess any adverse event or any other condition that the principal investigator considers vital to assess.
- Telephone or email evaluations (+/- 7 days): The purpose of this evaluation is to assess and document AEs. These will occur at week 1, week 4, week 13, week 19, week 23, week 31, week 38, week 44, week 55, and week 75.

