### **3.5 Safety and Tolerability**

Monitoring for safety after administration of undifferentiated MSC focus on acute hypersensitivity reaction and a sub-acute or delayed antibody-mediated reaction that can occur within 3-4 weeks of the infusion. A primary concern, although extremely rare, in MSC infusion therapy is the development of a hypersensitivity reaction. Transient (lasting several hours) fever is the most common but again rare administration side effect. An acute, more serious hypersensitivity reaction causing fever, confusion, kidney, liver, or other organ damage, hemolytic anemia or pneumonitis has a very low risk of occurrence. Additionally, the systemic or intravenous route of administration means that the MSC can be distributed to many different tissues and organs in the body and we know that most will end up in pulmonary tissue and that the small molecules will distribute throughout the circulation.

The immune privileged status of MSC has been demonstrated using expanded undifferentiated and differentiated MSC *in vitro* culture. The cell surface of these cells expresses intermediate levels of human leukocyte antigen (HLA) major histocompatibility complex (MHC) class I molecules and negligible levels of HLA class II and Fas ligand. There is no expression of the co-stimulatory molecules B7-1, B7-2, CD40 or CD40L, and when exposed to allogeneic lymphocytes, they fail to elicit a reactive response. However, with alloantibody production following repeated doses of MSC, no life-threatening host vs. graft responses have been reported.

Lalu *et al* reviewed the safety of systemic MSC administration in humans in a meta-analysis of 36 studies. Based on these analyses, MSC therapy appears safe with transient fever as the only significant administration side effect.

To prove the safety and feasibility of the use of intravenously deliver allogeneic bone marrow-derived MSCs in patients with PD, our group designed and conducted the first USA single-center open-label dose-escalation phase 1 study and we demonstrated that a single infusion of allogeneic

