## Appendix O. Telephone Evaluation

Patient ID: MSCII-PD-\_\_\_\_\_

Date of Phone Call: \_\_\_\_/\_\_\_\_/\_\_\_\_

| Contact Information |                         |                |
|---------------------|-------------------------|----------------|
| Patient Phone:      | Alternate Phone Number: | Patient Email: |
|                     |                         |                |

Please circle the specific time point:

| Infusion 1                                          |                                                             |                                                        |                    |
|-----------------------------------------------------|-------------------------------------------------------------|--------------------------------------------------------|--------------------|
| 3-7 days post, week 1
(After Infusion #1) | 21-35 days post, week 3-5
(Before S&C Assessment) | 70 days post, week 10
(After S&C Assessment) | Unscheduled |

| Infusion 2                                      |                                                              |                                                         |
|-------------------------------------------------|--------------------------------------------------------------|---------------------------------------------------------|
| 3-7 post, week 14
(After Infusion #2) | 21-35 day post, week 16-18
(Before S&C Assessment) | 161 days post, week 23
(After S&C Assessment) |

| Infusion 3                                           |                                                                 |                                                                 |                                                                 |
|------------------------------------------------------|-----------------------------------------------------------------|-----------------------------------------------------------------|-----------------------------------------------------------------|
| 3-7 days post, week 27
(After infusion #3) | Day 238-252 post, week 34-36
(After S&C Assessment 1) | Day 308-329 post, week 44-47
(After S&C Assessment 2) | Day 420-452 post, week 60-66
(After S&C Assessment 3) |

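### Post-infusion safety calls are fixed to study weeks while infusions 2 and 3 can move by a week, and the call form still carries an older schedule

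*Protocol*

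**What the plan says.** **Calls.** Section 10 lists ten evaluations: at weeks 1 and 4, then "week 13, week 19, week 23, week 31, week 38", then at weeks 44, 55 and 75. It introduces them as "Telephone or email evaluations (+/- 7 days" (closing bracket omitted), and section 10.2 repeats the weeks. Neither section ties a call to the date on which an infusion was given.

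**Infusions.** Section 10 has "Visit #5 Infusion Day (week 18+/-1 week): Second IV MSCs infusion" and "Visit #7 Infusion Day (week 36+/-1 week): Third IV MSC infusion".

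**Call form.** In Appendix O the first call after infusion 2 is labelled "3-7 post, week 14", and the first after infusion 3 is labelled "3-7 days post, week 27". The second call after infusion 2 is set at 21 to 35 days and labelled weeks 16 to 18.

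**Risk being watched.** Section 3.5 says that monitoring focuses on acute hypersensitivity and on "a sub-acute or delayed antibody-mediated reaction that can occur within 3-4 weeks of the infusion".

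**Unscheduled visit.** Section 10 describes it as "Unscheduled visit (between 2 to 15 days after reporting a non-live treating AE related to the MSC infusion" (closing bracket omitted), and its stated purpose is full assessment of adverse events. In the schedule table its column marks only the examination with medication review, and vital signs. The cells for CBC/CMP and donor-specific antibodies (DSA) are blank. Section 12.4 counts laboratory tests among the sources of adverse-event information at every clinic visit.

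**The concern.** A call meant to follow up an infusion should not be able to come before it. Here it can for infusion 2, because the call and the infusion have separate windows around separate study weeks. The form that staff complete adds a second conflict, since its week labels belong to a different infusion schedule.

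The calls are the only scheduled safety contacts in the first weeks after infusions 1 and 2. If their timing drifts, early events are picked up later or recalled less well, and unevenly from one infusion to the next. Section 16 also has the DSMB review aggregate data one month after each infusion. With dates on time, the week-19 call is the only scheduled contact completed by then after infusion 2.

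**Working it through.** **Inputs (section 10).** Infusion 1 is week 0. Infusion 2 is at weeks 17 to 19, infusion 3 at weeks 35 to 37. Calls run from 1 week before to 1 week after their stated week. Clinical visits have a window of 1.5 weeks either way.

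**Count of calls.** The list in section 10 has 10 entries, as that section states. Appendix O also has 3 + 3 + 4 = 10, leaving out its unscheduled option.

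**Lag after infusion, in weeks.** Earliest lag = earliest contact − latest infusion. Latest lag = latest contact − earliest infusion.

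| Contact | Infusion | Nominal | Earliest | Latest |
|---|---|---|---|---|
| Call, week 1 | 1 | 1 | 0 | 2 |
| Call, week 4 | 1 | 4 | 3 | 5 |
| Call, week 19 | 2 | 19 − 18 = 1 | 18 − 19 = −1 | 20 − 17 = 3 |
| Call, week 23 | 2 | 23 − 18 = 5 (day 35) | 22 − 19 = 3 | 24 − 17 = 7 |
| Call, week 38 | 3 | 38 − 36 = 2 (day 14) | 37 − 37 = 0 | 39 − 35 = 4 |
| Visit 4 (CBC/CMP, DSA) | 1 | 9 | 7.5 | 10.5 |
| Visit 6 (CBC/CMP, DSA) | 2 | 27 − 18 = 9 | 25.5 − 19 = 6.5 | 28.5 − 17 = 11.5 |
| Visit 8 (CBC/CMP, DSA) | 3 | 40 − 36 = 4 | 38.5 − 37 = 1.5 | 41.5 − 35 = 6.5 |

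After infusion 2, nominal contacts fall at 1, 5 and 9 weeks, with laboratory tests only at the last. Infusion 1 has a call at 4 weeks, and infusion 3 has a clinic visit with laboratory tests at 4 weeks.

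**How often the week-19 call could come first.** Assume that both dates are independent and uniform in their windows; the protocol gives no such distribution. The windows overlap in weeks 18 to 19, so the probability is (1 × 1 ÷ 2) ÷ (2 × 2) = 0.125.

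**Infusion weeks implied by Appendix O.**
- Infusion 2: 14 − 1 = 13; 16 − 3 = 13; 18 − 5 = 13. All three give week 13, against week 18 now.
- Infusion 3: 27 − 1 = 26, against week 36 now.
- Week 14 minus the current infusion 2 runs from 14 − 19 = −5 to 14 − 17 = −3 weeks.
- Weeks 16 to 18 run from 16 − 19 = −3 to 18 − 17 = +1 week.
- Week 27 minus the current infusion 3 runs from 27 − 37 = −10 to 27 − 35 = −8 weeks.

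**Form days against section 10.** For infusion 1 the second call agrees exactly: week 4 with its window is days 21 to 35. For infusion 3 given on time, the week-38 window is days 7 to 21, so only day 7 also meets the form's 3 to 7 days. If infusion 3 is given at week 35, the window is days 14 to 28 and no date meets both. The form also mixes starting points: its 161-day entry under infusion 2 is 161 ÷ 7 = 23 weeks, counted from infusion 1.

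**Other traces of an older schedule.** The Appendix E footnote puts visits 4, 6 and 8 at weeks 7, 20 and 29, where section 10 has 9, 27 and 40. Section 11.2 speaks of DSA at week 8 or 21. Section 13.1 ends participation at week 78, where section 10 has 88.

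**The case against.** **The early call is a corner case.** It needs a late infusion and an early call. Section 10.2 says that the calls monitor patients after an infusion visit, and the form labels the entry as following infusion 2, so a sensible coordinator would wait. This limits how often it happens. It does not remove the conflict: a coordinator who follows the form's days for infusion 3 will usually leave the section 10 window.

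**A late call does not erase an event.** Appendix O records start and stop dates, later visits collect adverse events, and ongoing events are reviewed again. Patients are told to report events at once and receive a red-flag sheet. The limit in section 3.5 is an upper bound, so a call at 5 weeks can still capture a delayed reaction in retrospect. All of this stands. A reader might infer that delayed reactions will go unseen, but the documents make delay or weaker recall likelier than a complete miss.

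**No bias between arms follows.** A reader might infer that uneven follow-up distorts a trial that compares numbers of MSC infusions. But every patient in every arm receives three blinded infusions on one schedule with one call list. Weaker ascertainment after infusion 2 affects MSC and placebo alike. This stands too.

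**Blank laboratory cells do not forbid tests.** A reader might infer that a suspected reaction would be worked up without laboratory tests. The table fixes no panel for the unscheduled visit, while sections 10 and 12.4 point towards testing. The allergic-reaction and DSA algorithms are figures not shown here and may say more. Only an inconsistency is established.

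**Conclusion.** The point holds as an internal contradiction in the safety-call schedule. With all dates in window, the week-19 call falls from 1 week before to 3 weeks after infusion 2, the week-23 call 3 to 7 weeks after it, and the week-38 call 0 to 4 weeks after infusion 3. The Appendix O week labels fit a different schedule, and its printed days do not match section 10.

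The consequence is moderate: later or less complete ascertainment, mainly after infusion 2, where no call is nominally due between 1 and 5 weeks and laboratory tests are not due until about 9 weeks. The lags assume that calls are counted from infusion 1, as written, and are not moved when a later infusion moves. The 12.5% figure rests on the uniform model and is only an illustration.

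The unscheduled-visit column is a separate and smaller inconsistency between the schedule table and sections 10 and 12.4.

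**What to change.** - In sections 10 and 10.2 and Appendix O, define each post-infusion call relative to the patient's actual infusion date, so that no call can precede the infusion it follows up.
- Reconcile the day offsets with the study weeks across those three places. The sponsor must decide which timing is intended.
- Remove the outdated week labels from Appendix O and state one starting point for every day count. Correct the related week numbers in Appendix E and sections 11.2 and 13.1 at the same time.
- Reconcile the unscheduled-visit column of the schedule table with the purpose given in section 10 and with section 12.4. This review does not propose which tests belong there.

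The cost is a wording amendment and a reissued form. The number of calls stays at ten.

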## 10.1 Clinical visits

### 10.1.1 Screening visit: (Visit 1= between weeks -12 and -3)

Patients will be screen in numerical order based on their assigned number. This visit will take approximately 3-4 hours.

Prior to performing any study activity, the subject will be thoroughly informed on all aspects of the study, including all scheduled visits, activities, and procedures, and will be requested to sign and date the IRB approved informed consent form.

The following procedures and evaluations are to be performed at Screening visit:

- Obtain written informed consent.
- Subject ID Number assigned (2 digits number starting at 01)
- Obtain Vital Signs (orthostatic blood pressure, respiration, oxygen saturation, heart rate, temperature, weight, height).
- Obtain a 12 lead Electrocardiogram (EKG)
- Obtain Demographic information.
- Medical History.
- Obtain socio-economic information.
- Obtain smoking, alcohol & caffeine information.
- Review and document concomitant medications.
- Document PD diagnosis date and PD Features.
- Assess primary diagnosis/probability of PD.
- Perform general Physical Exam: general appearance, head, eyes, ears, nose, neck, and throat, lungs, heart, peripheral pulses, and skin.

- Perform a complete neurological exam: orientation to self, time and place, speech observation, cranial nerves, strength, sensory, reflexes, gait, and cerebellar.
- Perform the MDS-UPDRS (Movement Disorders Society Unified PD Rating Scale). The MDS-UPDRS scale will be performed first OFF medication and then ON medication (For this assessment, patients will be asked to hold their current PD treatment for 12 hours prior to the visit). The MDS-UPDRS-III will be videotaped for rating assessment by the other two movement disorder specialists.
- Assess H&Y (Hoehn and Yahr scale).
- Measure TUG (Timed Up and Go Test).
- Administer MoCA (Montreal Cognitive Assessment).
- Provide UPSIT (University of Pennsylvania Smell identification test) for self-administration.
- Provide ADL (Schwab and England Activities of daily living score) for self-administration.
- Administer the Lifetime/Recent version of the Columbia–Suicide Severity Rating Scale (C-SSRS).
- Provide EQ-5D-5L (EuroQol- 5Dimension).
- Provide GDS-SF (Geriatric Depression Scale Short form).
- Provide PAS (Parkinson Anxiety Scale).
- Provide PDQ-39 (Parkinson's Disease Questionnaire) for self-administration.
- Provide RBD-Single-Question Screen (RBD1Q).
- Urine sample for Dipstick urinalysis.
- Collect a blood sample for laboratory screening:
  - Complete blood count (CBC) with differential.
  - Comprehensive Metabolic Panel.
  - Specialty Blood Chemistry.
- Vascular access assessment
- Lumbar access assessment
- Assess the need for change in symptomatic therapy.

A week after this visit, the principal investigator will assess subjects for study eligibility based on all inclusion/exclusion criteria, including the laboratory results and will determine if the patient will be enrolled in the study.

### 10.1.2 Baseline visit (Visit 2= between week -11 to week-1)

This visit will take approximately 6-7 hours. The following procedures and evaluations are to be performed at baseline:

- Performed Neuroimaging in the levodopa OFF state:
  - High-resolution T1- & T2-weighted MRI.
  - Perfusion MR.

- Diffusion-weighted MRI.
- Neuromelanin MRI.
- Collect blood samples for:
  - DSA (Donor specific antibodies). Order as HLA typing.
  - Peripheral markers: Neurotransmitters, Oxidative stress, cytokines, chemokines, and growth factors.
  - $\alpha$ -synuclein oligomers levels.
- Collect urine sample for  $\alpha$ -synuclein oligomers
- Performed Lumbar Puncture and observe for 2 hours.
- CSF samples for:
  - CBC with differential.
  - Glucose and Protein levels
  - $\alpha$ -synuclein oligomers
  - Markers: Neurotransmitters, Oxidative stress, cytokines, chemokines and growth factors.
- Provide verbal and written instruction regarding the infusion visit and explain the procedure to the patient.
- Obtain vital signs before discharge (blood pressure, respiration, oxygen saturation, heart rate, and temperature).

**10.1.3 Infusion visits:** (*Visit 3*= Week 0; *Visit 5*=Week 18+/-1 week; *Visit 7*=Week 36+/-1 week)

This visit will take approximately 5-6 hours. The following procedures and evaluations are to be performed at Infusion visit:

- Explain the procedure to the patient, including the 4-hour monitoring period.
- Obtain Vital Signs (blood pressure, respiration, oxygen saturation, heart rate, and temperature).
- If the urine sample was not collected during the baseline, please collect the sample at this visit. Review and document concomitant medications
- Perform general Physical Exam: general appearance, head, eyes, ears, nose, neck, and throat, lungs, abdomen, heart, peripheral pulses and skin.
- Perform a complete neurological exam: orientation to self, time and place, speech observation, cranial nerves, strength, sensory, reflexes, gait, and cerebellar.
- Infusion procedure: The study patient will take their regular PD meds on the infusion day and arrive by 8:00 am. After obtaining vital signs and performing a general and neurological examination, two IV lines will be started. MSCs will be infused according to the description provided in section 7.3. Vitals signs will be obtained at the end of the infusion.

- 4-hour monitoring period: After the infusion patients will be monitored for 4 hours. Vital signs will be checked 1 hour after the infusion, 2 hours after the infusion, and before discharge. A complete physical and neurological exam will be done before discharge.
- Provide written information regarding red flags. (*See Appendix N for a copy of Red Flags*).

Subjects will be instructed to immediately report any adverse events to the Coordinator after their departure.

**10.1.4 Clinical and Safety Assessment:** (*Visit 4* = week 9+/-1.5 week; *Visit 6* = week 27+/-1.5 week and *Visit 8* = week 40+/-1.5week; *Visit 9*=week 49+/-1.5 week; *Visit 10*=week 62+/-1.5 week)

This visit will take approximately 3-4 hours. The following procedures and evaluations are to be performed at Clinical and Safety Assessment visits:

- Obtain Vital Signs (orthostatic blood pressure, respiration, oxygen saturation, heart rate, temperature, weight). (All visits except visit 9)
- Review and document concomitant medications.
- Perform general Physical Exam: general appearance, head, eyes, ears, nose, neck, and throat, lungs, heart, peripheral pulses and skin.
- Perform a complete neurological exam: orientation to self, time and place, speech observation, cranial nerves, strength, sensory, reflexes, gait, and cerebellar.
- Assess MDS-UPDRS (Movement Disorders Society Unified Parkinson's disease Rating Scale). The MDS-UPDRS-III will be videotaped for rating assessment by the other two movement disorder specialists. (All visits except visit 9)
- Assess H&Y (Hoehn and Yahr scale). (All visits except visit 9)
- Assess TUG (Timed Up and Go Test). (All visits except visit 9)
- Administer MoCA (Montreal Cognitive Assessment). (**Only at visit 9**)
- Provide UPSIT (University of Pennsylvania Smell identification test) for self-administration. (**Only at visit 9**). This will be sent to the patient home address one week before visit 9. Each patient will complete the test at home and bring it for visit 9. Administer the Since last time version of the Columbia–Suicide Severity Rating Scale (C-SSRS). (All visits except visit 9)
- Provide ADL (Schwab and England Activities of daily living score) for self-administration.
- Provide EQ-5D-5L (EuroQol- 5Dimension). (All visits except visit 9)
- Provide GDS-SF (Geriatric Depression Scale Short form). (All visits except visit 9)
- Provide PAS (Parkinson Anxiety Scale). (All visits except visit 9)
- Provide PDQ-39 (Parkinson's Disease Questionnaire) for self-administration. (All visits except visit 9)
- Collect blood samples for:
  - DSA (Donor specific antibodies). Order as HLA typing. (**All visits except visit 9 & 10**)

- Peripheral markers: Neurotransmitters, Oxidative stress, cytokines, chemokines, and growth factors. (*All visits except visit 10*)
- $\alpha$ -synuclein oligomers levels. (*Only at visit 8 & 9*)
- Performed Neuroimaging in the levodopa OFF state (*Only at visit 8*):
  - High-resolution T1- & T2-weighted MRI.
  - Perfusion MR.
  - Diffusion-weighted MRI.
  - Neuromelanin MRI.
- Performed Lumbar Puncture and observe for 2 hours (*Only at visit 9*)
- Collect urine sample for  $\alpha$ -synuclein oligomers (*Only at visit 9*)
- CSF samples for:
  - CBC with differential.
  - Glucose and Protein levels
  - $\alpha$ -synuclein oligomers
  - Markers: Neurotransmitters, Oxidative stress, cytokines, chemokines, and growth factors.
- Review DSA results from the previous visit. (*Only at visit 4 & 6*):
- Assess the Need for change in symptomatic therapy.

